## Abstract

**Background:**

Tobacco use remains the number one cause of preventable chronic disease and death in developed countries worldwide. In North America, smoking rates are highest among young adults. Despite that the majority of young adult smokers indicate wanting to quit, smoking rates among this age demographic have yet to decline. Helping young adults quit smoking continues to be a public health priority. Digital mobile technology presents a promising medium for reaching this population with smoking cessation interventions, especially because young adults are the heaviest users of this technology.

**Objective:**

The primary aim of this trial is to determine the effectiveness of an evidence-informed mobile phone app for smoking cessation, Crush the Crave, on reducing smoking prevalence among young adult smokers.

**Methods:**

A parallel randomized controlled trial (RCT) with two arms will be conducted in Canada to evaluate Crush the Crave. In total, 1354 young adult smokers (19 to 29 years old) will be randomized to receive the evidence-informed mobile phone app, Crush the Crave, or an evidence-based self-help guide known as “On the Road to Quitting” (control) for a period of 6 months. The primary outcome measure is a 30-day point prevalence of abstinence at the 6-month follow-up. Secondary outcomes include a 7-day point prevalence of abstinence, number of quit attempts, reduction in consumption of cigarettes, self-efficacy, satisfaction, app utilization metrics, and use of smoking cessation services. A cost-effectiveness analysis is included.

**Results:**

This trial is currently open for recruitment. The anticipated completion date for the study is April 2016.

**Conclusions:**

This randomized controlled trial will provide the evidence to move forward on decision making regarding the inclusion of technology-based mobile phone interventions as part of existing smoking cessation efforts made by health care providers. Evidence from the trial will also inform the development of future apps, provide a deeper understanding of the factors that drive change in smoking behavior using an app, and improve the design of cessation apps. This trial is among the first to assess the effect of a comprehensive and evidence-informed mHealth smoking cessation app on a large sample of young adult smokers. Strengths of the trial include the high-quality research design and in-depth assessment of the implementation of the intervention. If effective, the trial has the potential to demonstrate that including mHealth technology as a population-based intervention strategy can cost-effectively reach a greater proportion of the population and help young adult smokers to quit.

**Trial Registration:**

ClinicalTrials.gov NCT01983150; http://clinicaltrials.gov/ct2/show/NCT01983150 (Archived by WebCite at http://www.webcitation.org/6VGyc0W0i).

## Introduction

### Background

Tobacco use remains the number one cause of preventable chronic disease and death in developed countries worldwide [1]. Currently, young adults represent the largest population of smokers across North America [2,3], and this age demographic is particularly vulnerable to the negative health effects of tobacco use [4-9]. Although smoking prevalence increases from adolescence into adulthood, most young adult smokers express a desire to quit. For example, Canadian young adults aged 20 to 24 and 25 to 34 who smoked reported that they were seriously considering quitting in the next 6 months at a prevalence of 61.7% and 71.5%, respectively [2]. Given evidence that quitting before the age of 40 reduces the risk of a tobacco-related death by as much as 90% [10], and that quit attempts decrease with age as patterns of tobacco use become engrained [2], helping young adults successfully quit smoking is a priority.

Finding effective solutions to help young adults quit smoking remains a challenge. Despite the existence of a myriad of evidence-based smoking cessation options [11], research suggests that younger adult smokers are particularly unlikely to seek treatment compared to older smokers [12-14]. For example, according to a survey investigating the use of cessation treatments, young adults aged 18 to 24 were half as likely to have used pharmacological (eg, nicotine replacement therapy NRT) or psychological (eg, advice from a health professional) treatments to aid with cessation as were older adults [14]. The underutilization of smoking cessation interventions by young adults combined with a lack of age-appropriate cessation interventions [15] and comprehensive marketing to younger populations by the tobacco industry [16] are major reasons for the lack of declines in young adult smoking rates. New strategies for reaching young adult smokers are needed. Recently, digital technologies have emerged as promising platforms to enhance tobacco control efforts directed toward this population [17].

Digital technologies have become ever more pervasive in young adults’ everyday lives. According to recent statistics, young adults aged 18 to 29 lead the way in the use of mobile phones, both those that run apps (65%) and those that do not (93%) [18]. The use of mobile phone apps has become a focused means for engaging young adults. Not only are young adults most likely to download apps, but they are also the most intense users of apps [19]. It is not surprising, then, that young adults are the most frequent users of health-related apps. It has been reported that 42% of those who seek health information through apps are young adults [20]. In addition, researchers have alluded to a trend toward increased use of mobile phones among lower socioeconomic status groups [21], increasing the likelihood of successfully delivering mobile phone-based health improvement interventions to traditionally hard-to-reach populations [22].

The use of mobile phone apps for health interventions, such as for smoking cessation, offers many unique benefits compared to traditional approaches, most notably because individuals can access these interventions anytime and in everyday settings [23] since assistance is immediately available when needed (eg, help in dealing with cravings). In addition, individuals have many opportunities to tap into various support networks [24] via their mobile phones, such as through social media. Support networks include those which are intervention related (eg, quit buddies and social networking sites associated with the intervention) and those related to their personal social networks (eg, personal contacts). In fact, social networks have been found to play a key role in young adults’ smoking cessation success [13,25,26]. Furthermore, the increasing use of internal sensors in mobile phones provides reliable contextual data that can infer such things as geographical location and has enabled tracking of health behaviors, as well as the delivery of interventions that are tailored to specific contexts [24]. These features enabled by mobile phones are a clear advancement over websites and short message service (SMS) text messaging programs. Their high potential to boost user engagement [27] has been consistently documented as a strong predictor of smoking cessation [28-30].

There is a growing body of evaluative evidence demonstrating that mobile phone-based technologies can support smoking cessation. However, most of this evidence consists of studies evaluating the efficacy of mobile phone SMS text messaging interventions for smoking cessation [31]. Young adults have reported an interest in more intense mobile-based smoking cessation interventions, such as mobile phone apps, versus what is currently offered via SMS text messaging, [12,32,33]. Mobile phone apps have the ability to enrich the user experience with more information, components, and functionality [34]. As well, smoking cessation mobile phone apps now have enormous reach compared to quitlines and SMS text messaging interventions [27]. For these reasons, exploring the effectiveness of mobile phone apps is critical. Only two randomized controlled trials (RCTs) were found that evaluated the efficacy of a smoking cessation mobile phone app. One compared a mobile phone app to an SMS text messaging intervention for smoking cessation [35]. It was reported in this study that both the mobile phone app and the SMS text messaging intervention predicted a significant increase in 30-day abstinence at 12 weeks [35]. Another pilot study tested the efficacy of a smoking cessation app based on acceptance and commitment therapy and found that it was feasible to deliver a theory-based mobile phone app with quit rates higher than the control condition [27]. Many mobile phone apps for smoking cessation exist that have the potential to integrate education, motivational techniques, quit plan assistance, linkages to support networks, quit coaches, and other functionalities that go beyond SMS text messaging [36]. Despite these functionalities, a recent systematic review reported that very few studies have been conducted to measure the outcomes of these apps, especially long-term outcomes [31]. A methodologically rigorous evaluation of mobile phone cessation technology is an identified gap in the published literature. The findings from this randomized controlled trial (NCT01983150) will help address this gap by determining whether mobile phone apps work for quitting and, more importantly, why they do or do not work. This is critical in light of an increasing push for mHealth scale-up [37].

### Study Aims

The primary aim of this study will be to determine the effectiveness of the evidence-informed mobile phone app for smoking cessation, Crush the Crave, on reducing smoking prevalence among young adult smokers after 6 months. Crush the Crave was developed by an expert team based at the University of Waterloo who worked with a technology development team to design, prototype, evaluate, and revise the program over the course of 2 years. This study will represent the first full trial of the program as part of a population-level intervention. We expect that individuals randomized to the evidence-informed mobile phone intervention condition will have higher 30-day point prevalence quit rates than individuals assigned to the control condition after 6 months.

Secondary aims of this study include the following:

1. Examine more proximal outcome measures of cessation behavior, including 7-day point prevalence abstinence (PPA), time to cessation, the number of quit attempts, and the reduction in consumption of cigarettes.

2. Examine satisfaction and patterns of app use at 3 and 6 months, including the extent to which it promotes the use of established smoking cessation services, such as nicotine replacement therapy, health professional consults, medications, and quitline counseling.

3. Examine mediators of cessation outcomes between conditions, such as frequency of app use, use of cessation services, quit intentions, nicotine withdrawal, and the following psychosocial mediators: beliefs and attitudes, stress, social norms, self-efficacy, and perceived social support.

4. Compare the cost-effectiveness of the intervention and control conditions.

## Methods

### Design

This is a 6-month, two-arm, parallel randomized controlled trial (ClinicalTrials.gov Identifier: NCT01983150) to evaluate an mHealth intervention, Crush the Crave, for young adult smokers. Investigators and data collectors will be blinded to the group assignments. The protocol is in accord with the CONSORT-EHEALTH checklist [38]. See Figure 1 for a CONSORT-EHEALTH diagram of the proposed study design.

**Figure 1 figure1:**
[figure not shown]
CONSORT-EHEALTH diagram of the study design.

### Ethical Approval

The research methods to be used in this study have been approved by the Office of Research Ethics of the University of Waterloo (full ethics clearance granted on October 29, 2013, No. 19275).

### Study Population

Young adult male and female Canadian smokers are the target population for this study. Participants will be eligible for the study if they are between the ages of 19 and 29, are currently smoking cigarettes daily, are residing in Canada, are considering quitting smoking in the next 30 days, have an Android (version 2.0 to 5.0) or iPhone (version 4.0 to 7.0) OS mobile phone, are able to provide informed consent, are able to comprehend English, and have not been referred to the study by an existing study participant (eg, a friend or family member already participating in the study) to avoid possible contamination bias.

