### Recruitment

Recruitment will be staggered over 32 weeks and will include online recruitment through Facebook advertisements and Kijiji, an online classified message board, with offline recruitment through classified newspaper ads, and a Can $35 incentive for registering for the trial. Interested young adults will be referred to a website describing the trial. Potential participants will be screened at the entry webpage where their eligibility will be determined, informed consent will be sought, and registration for the trial will take place. A total of 1354 young adult smokers will be recruited. After providing informed consent and having completed the online baseline questionnaire, a computer-generated email message will be sent back to the participants confirming registration and participants will then be randomly allocated to either the control or intervention arm. The control group will participate in a usual care, self-help guide intervention called “On the Road to Quitting” [39] and the intervention group will participate in the Crush the Crave program.

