### Study Intervention

#### Overview

The intervention group will receive a comprehensive and evidence-informed smoking cessation mobile phone app, Crush the Crave, via the Internet. Crush the Crave enables users to customize a quit plan by choosing a quit date and then deciding whether to quit immediately or reduce the number of cigarettes they smoke every week up to their quit date. Crush the Crave then assists smokers in staying on track by reminding them of how much money they have saved and how much their health improves over time after quitting. Based on contingency reinforcement, these milestones are tracked as rewards, which smokers can then choose to share with their social network via Facebook and Twitter, and rally support from friends and family. Participants can also link to the Crush the Crave Facebook community for additional support for quitting. Users of the app also receive supportive text messages tailored to their specific quit plan and where they are in the quitting experience. Crush the Crave will allow the intervention group to track their daily smoking habits and cravings as well as understand their craving triggers or psychosocial determinants by recording when, where, and why they were smoking. The app provides both graphic and tabular performance feedback (see Figure 2). The app also provides online distractions to help smokers deal with their cravings. There are social media tools, such as a YouTube channel and opportunities to chat with friends online to distract a user until the craving subsides a few minutes later. Evidence-based information is available for assisting participants during the quitting experience on topics such as relapse and dealing with cravings. Furthermore, data are collected in real time to both support the user and to track the usage of the app allowing for push notifications, helpful reminders, and ongoing data collection. Finally, Crush the Crave provides access to evidence-based cessation services such as smoking cessation quitlines and explains the benefits of, and dispels myths around, nicotine replacement therapy.

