#### Development of Crush the Crave

Crush the Crave was developed in early 2012 by a team of population health researchers, social media experts, and computer programmers as an evidence-informed, quit-smoking mobile phone and social media app for young adults aged 19 to 29. In addition to the input of key experts in the field of smoking cessation, development of the app incorporated Fiore’s practice guidelines for treating tobacco use and dependence [44] and principles of persuasive technology for behavior change [45]. The app was tested in March 2012 with eight focus groups consisting of 57 male and female young adult smokers on functionality, look and feel, and usability. Young adult smokers were engaged in the design and the naming of the app. Furthermore, the app was pilot-tested by over 300 smokers from April to June 2012. The pilot test revealed substantial engagement with 319 users triggering 7931 events, including 1444 visits to the quit help page, 1415 visits to the awards page, and 1016 visits to the progress tracking page. The focus groups of young adult smokers provided positive feedback on app functionality and content. In light of evidence that existing smoking cessation mobile phone apps are not developed by health professionals or academics, do not draw on behavior change theories or techniques, and do not have content aligned to clinical guidelines and other evidence-based practices [22,46], Crush the Crave is a relatively novel intervention in the area of smoking cessation.

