### Data Collection

#### Baseline Questionnaire

Baseline data will be collected via a self-administered, online questionnaire completed by all consenting participants in both intervention and control groups. The baseline questionnaire will include the following demographic items: age, sex, ethnicity, marital status, education, income, and employment status. The following variables related to tobacco consumption will also be recorded: current smoking status, amount smoked, number and duration of past quit attempts, intentions to quit in the next 6 months, and the degree of nicotine dependence. Participants will also be asked a series of psychosocial questions, including beliefs and attitudes about quitting, self-efficacy or confidence in quitting, perceived stress and social support, and social norms related to smoking. Furthermore, participants will be asked about experience with mobile phone apps and self-help, use of NRT, and other cessation aids/supports, such as quitlines.

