#### Questionnaire for 3- and 6-Month Follow-Up

Follow-up data will be collected from the same participants at 3 and 6 months in the same manner as the baseline questionnaire. In addition to the questions asked at baseline, participants will be asked core smoking status questions, including whether they have smoked any cigarettes or used other tobacco products, even a puff, in the last 30 days, 7-day point prevalence abstinence, number of quit attempts, and the reduction in cigarette consumption. Participants will then be asked questions on nicotine withdrawal, level of support received from friends and family for quitting smoking, additional cessation services that they sought for helping to quit, overall satisfaction with the app or self-help guide, use of the app or guide, opinions and beliefs about the app or guide, and challenges they experienced in quitting smoking. A modified Dillman method [52] for the online survey questionnaires will be used and up to 10 attempts (email and telephone) will be made to reach participants if they do not complete the online questionnaire within 2 weeks of the 3- and 6-month follow-up periods. Questionnaires will be pilot-tested with a convenience sample of young adult smokers.

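### Contamination is guarded against only by the referral rule: earlier Crush the Crave users stay eligible, and the article does not secure measurement of app use among controls

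*Protocol article*

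**What the plan says.** Under Study Population, the protocol article lists its entry criteria and includes one rule against contamination: participants must "have not been referred to the study by an existing study participant". The same list requires every participant, controls included, to "have an Android (version 2.0 to 5.0) or iPhone (version 4.0 to 7.0) OS mobile phone". It contains no criterion on use of Crush the Crave.

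The app predates the trial. Under Development of Crush the Crave, the article reports that "the app was pilot-tested by over 300 smokers from April to June 2012", and gives 319 users with recorded events.

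After entry, participants know their arm (Randomization and Blinding). The app tracks rewards "which smokers can then choose to share with their social network via Facebook and Twitter" and links to its own Facebook community (Study Intervention, Overview). Recruitment includes "online recruitment through Facebook advertisements and Kijiji".

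On measurement, the Baseline Questionnaire section says that "participants will be asked about experience with mobile phone apps and self-help, use of NRT, and other cessation aids/supports, such as quitlines". The follow-up section repeats the baseline questions at 3 and 6 months and adds "use of the app or guide, opinions and beliefs about the app or guide", along with other cessation services sought. Process Measures describes monitoring of downloads and a database of time-stamped app events, some tracked per user.

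**The concern.** The plan recognises the bias but closes only one route to it. A past or current Crush the Crave user can be randomised to either arm. In the control arm, such a person may carry over benefit from the app. In the app arm, the same person is not newly exposed. Either way the intention-to-treat difference moves toward zero.

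Controls also own a suitable phone, are considering quitting, and know that they were not given the app. If the app can be obtained outside the trial, some may look for it.

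The comparison depends on controls not having the app: under Standard Self-Help Condition, the guide was chosen because printed material is taken to do no better than no treatment. Study Aims also lists frequency of app use among the mediators to be examined between conditions, and that analysis needs app use established in both arms. If the result were null and control-arm use of this app had not been recorded, a reader would find it hard to judge whether dilution contributed.

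**Working it through.** **Inputs** (Sample Size and Power Calculations): two-sided alpha 0.05, power 80%, 1:1 allocation; 11% v 17% abstinent; after 20% attrition with non-responders counted as smokers, 8.8% v 13.6%; 677 per arm. Attrition is the only allowance made.

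**1. Reproduce the plan's sample sizes.** Pooled-variance formula, no continuity correction, with p̄ the mean of the two rates:

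n = [1.960·√(2p̄(1−p̄)) + 0.842·√(p₁(1−p₁) + p₂(1−p₂))]² / (p₂−p₁)²

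- 11% v 17%: (1.960·√0.2408 + 0.842·√0.2390)² / 0.06² = 523.8, so 524 per arm.
- 8.8% v 13.6%: (1.960·√0.1989 + 0.842·√0.1978)² / 0.048² = 676.4, so 677 per arm.

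Both match the article. Power at 677 per arm is 80.0%, so there is no slack.

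**2. Dilution through the control arm.** Let c be the share of controls who gain the full app effect. The control rate becomes 8.8% + c × 4.8 points, and

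power = Φ{[(p₂−p₁)·√677 − 1.960·√(2p̄(1−p̄))] / √(p₁(1−p₁) + p₂(1−p₂))}

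For c = 5%: p₁ = 9.04%, difference 4.56 points; (0.0456 × 26.02 − 1.960·√0.2008) / √0.1997 = 0.69, and Φ(0.69) = 75.5%.

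| c (assumed) | Control rate | Power at 677 per arm | n per arm for 80% |
|---|---|---|---|
| 0% | 8.80% | 80.0% | 677 |
| 2% | 8.90% | 78.3% | 708 |
| 5% | 9.04% | 75.5% | 757 |
| 10% | 9.28% | 70.5% | 852 |

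**3. Dilution through the app arm.** Suppose instead that earlier users get no benefit in either arm. A share f then lowers the app-arm rate to 13.6% − f × 4.8 points. Power is 78.6% at f = 2%, 76.3% at 5% and 72.1% at 10%. This is an alternative to step 2, not an addition to it.

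**4. How much could the documented pilot pool supply?** Of 1354 participants:

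- 2% is about 27 people, or 27/319 = 8% of the pilot users.
- 5% is about 68, or 21%.
- 10% is about 135, or 42%.

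They would also have to be daily smokers aged 19 to 29 and living in Canada when they enrol. The pilot group alone therefore cannot plausibly produce the 10% row. That row would need access to the app beyond the pilot, on which the article is silent.

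**The case against.** A reader might infer that app use in the control arm is never asked about and that dilution would go unseen. The text does not support that. The app-experience item goes to both arms and is repeated at follow-up. Use of the app or guide is asked of participants without being tied to an arm, although it can be read as each arm's own product. The examples of cessation services are illustrative, not a closed list, and app events are logged per user. Exact item wording belongs to the questionnaire, which is not shown, so its absence from an article is not in itself a fault.

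The size can also be challenged. Giving every exposed control the full effect is a worst case: a pilot user who still smokes daily at entry is a poor candidate for it, and seeing a shared reward on Facebook is not the same as receiving the programme. The documented pool is small. Use of other quit-smoking apps by controls can fairly count as usual care.

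These points stand, and they limit the claim about measurement and its likely size. They do not touch the entry rule. The article sets out its criteria and its contamination safeguard, and that safeguard leaves earlier users of the trial's own app eligible.

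**Conclusion.** The point holds in a limited form. The referral rule is the only stated guard, current and previous Crush the Crave users can enrol, and the sample size makes no allowance for cross-over. Whether dilution would be measured is unclear: the article does not say that controls are asked specifically about this app or that usage records are checked for them.

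Power would fall from 80.0% to 78.3%, 75.5% and 70.5% at 2%, 5% and 10% exposure. These figures rest on the article's own rates, on the full app effect in every exposed control, and on exposure shares that are assumed. Prior use from the documented pilot alone points to the low end of that range. The higher figures should not be read as forecasts.

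It would also go too far to conclude that a null result could not be interpreted, because the questions and logs that are described may capture some cross-over. The gap is not fatal, but it biases toward no difference and is inexpensive to close.

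**What to change.** 1. Add previous or current use of Crush the Crave as an exclusion on the web eligibility screen. Recruitment is already open, so for those already enrolled, record use before enrolment at follow-up.
2. At 3 and 6 months, ask both arms the same items on use of Crush the Crave and of the self-help guide. List them among other cessation aids so that controls are not pointed to the app.
3. State whether the app can be obtained outside the trial and whether usage records will be checked for controls.
4. Report cross-over by arm and keep intention-to-treat as the primary analysis. A complier-average estimate as a sensitivity analysis, and an item on other quit-smoking apps, are optional.

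The cost is one screening item and a few follow-up items in questionnaires that the article says will be pilot-tested. A few otherwise eligible smokers would be excluded, and a small risk of alerting controls to the app remains even with a mixed list.
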